# Early detection of health problems in potentially frail community-dwelling older people by general practices - project [G]OLD: design of a longitudinal, quasi-experimental study

**DOI:** 10.1186/1471-2318-13-7

**Published:** 2013-01-18

**Keywords:** Frailty, Older people, Comprehensive geriatric assessment, Home visit, General practice, Quasi-experimental design

## Abstract

**Background:**

Due to the ageing of the population, the number of frail older people who suffer from multiple, complex health complaints increases and this ultimately threatens their ability to function independently. Many interventions for frail older people attempt to prevent or delay functional decline, but they show contradicting results. Recent studies emphasise the importance of embedding these interventions into existing primary care systems and tailoring care to older people’s needs and wishes. This article presents the design of an evaluation study, aiming to investigate the effects and feasibility of the early detection of health problems among community-dwelling older people and their subsequent referral to appropriate care and/or well-being facilities by general practices.

**Methods/Design:**

A longitudinal, quasi-experimental study is designed comparing 13 intervention practices with 11 control practices. General practices select eligible community-dwelling older people (≥ 75 years). Practice nurses from intervention practices (1) visit older people at home for a comprehensive assessment of their health and well-being; (2) discuss results with the GP; (3) formulate – if required – a care and treatment plan together with the patient; (4) refer patient to care and/or well-being facilities; and (5) monitor and coordinate care and follow-up. Control practices provide usual care and match the intervention practices on the presence of different primary care professionals within the practice. Primary outcome measures are health-related quality of life and disability. Additionally, attitude towards ageing, care satisfaction, health care utilisation, nursing home admission and mortality are measured. Some outcomes are assessed by means of a postal questionnaire (at baseline and after 6, 12, and 18 months follow-up), others through continuous registration over the 18-month period. A profound process evaluation will provide insight into barriers and facilitators for implementing the intervention protocol within general practices from both the patient and caregiver perspective.

**Discussion:**

The proposed approach requires redesigning care delivery within general practices for accomplishing appropriate care for older people. A quasi-experimental design is chosen to closely resemble a real-life situation, which is desirable for future implementation after this innovation proves to be successful. Results of the effect and process evaluation will become available in 2013.

**Trial registration:**

The Netherlands National Trial Register NTR2737

## Background

Ageing of the population poses challenges to health care systems as the number of frail older people who suffer from complex and/or multiple (chronic) health complaints increases [1,2]. A failure to detect health complaints among older people in time may cause unnecessary neediness and may threaten their ability to function independently.

Strategies comprising early identification of older people at risk of poor health and early intervention should prevent or postpone the onset of functional decline and maintain independent living [3]. In the last decades, there has been an increased focus worldwide on the development of preventive home visitation programmes to support older people to grow old at home and to prevent or delay institutionalisation.

There is still an ongoing debate whether these preventive home visits should be part of regular care for older people. Numerous systematic reviews have been published [4-11], attempting to determine the effectiveness of preventive home visits, but the results remain inconclusive. Discrepancy in the results is caused, among others, by differences in the selection of the target population, intensity and duration of the intervention (i.e., number of follow-up visits), or domains included in the multidimensional assessment of older people’s health status [12]. Thus, the question remains which components of preventive home visits are effective and for which population they are beneficial [13]. Most studies to date employ a randomised design for establishing the success of preventive home visits, thereby hindering close resemblance to a real-life situation and restricting the external validity of findings.

Recent publications stress the importance of integrating preventive interventions for older people into existing care systems [10,14,15]. For example, Van Hout and colleagues [14] attribute the absence of a preventive effect of home visits to the fact that they were not integrated within primary care practices. In our current approach, instead of solely integrating, we aim to redesign care delivery within primary care practices by applying components of the Chronic Care Model (CCM). This comprehensive framework has proven to lead to improved patient care and better health outcomes when changing routine delivery of care through improvements in six interrelated components (further details are provided in the Methods section) [16,17]. In addition, elements of the Guided Care model are incorporated in our approach [18]. Guided Care used the CCM to identify successful innovations in chronic care that can be applied in primary care to achieve optimal outcomes in people with chronic diseases and complex care needs.

General practices seem to be the ideal setting for realising preventive care facilities for older people, because of their geographical proximity to older people, knowledge of the patient’s medical history, relationship of trust between doctor and patient, and access to a range of multidisciplinary health care and well-being facilities in the person’s neighbourhood. However, general practitioners (GPs) often do not have a complete overview of the health status and functioning of older people [19,20]. A Dutch study among randomly selected older patients revealed that 34% of recorded health problems during a home visit were unknown to GPs (mostly psychosocial or physical complaints, such as depression and urine incontinence) [19]. Similarly, Alessi and co-workers [21] reported that three-quarter of the visited older people had at least one major health problem identified that was previously unknown. This suggests that a comprehensive geriatric assessment in the home setting yields important information about previously undetected health problems and this might be particularly beneficial for the *apparently* healthy older people.

It is equally important that older people themselves are aware of their own (unmet) health needs, as this appears to be supportive for maintaining independent living [22]. It seems that older people tend to discard certain health problems or complaints as inevitable aspects of ageing, such as in the case of urinary incontinence [23], they forget about the occurrence of certain events, such as in reporting falling incidents [24], or they may fail to recognise the significance of symptoms or complaints [25]. A multidimensional assessment may create awareness of these (unmet) needs or problems. After health problems and complaints are identified, care facilities should be tailored to older patient’s needs and preferences [26-28] and active involvement of older people in decision-making concerning their need for care services is encouraged [29].

In conclusion, we hypothesise that a multidimensional comprehensive geriatric assessment of the health and well-being of community-dwelling older people by general practices and subsequent individualised care and follow-up (if required) will lead to improved health-related quality of life and reduced disability compared to usual care (i.e., reactive care to older people who present themselves with health problems or complaints). Furthermore, we hypothesise that this approach will be feasible from both the patient and caregiver perspective. In the current paper, the design of an evaluation study is presented aiming to investigate the effects of identifying health problems and complaints among potentially frail community-dwelling older people at an early stage and, if necessary, their follow-up within care and/or well-being facilities. Parallel to the effect study, a process evaluation will provide insight into the barriers and facilitators for implementing the proposed approach within general practices.

## Methods/Design

### Study design and setting

The longitudinal, quasi-experimental study is performed in three regions in the south of the Netherlands: Maastricht-Heuvelland (8.5% ≥ 75 years), Parkstad (8.7% ≥ 75 years), and Midden-Limburg (7.5% ≥ 75 years). They are particularly interesting because the ageing of the population is more pronounced here (nationwide 7.0% ≥ 75 years). General practices in these regions were invited to participate in the evaluation study. Participating general practices randomly selected community-dwelling people aged 75 years and older from the GP Information System. Older people within intervention practices are visited at home by the practice nurse for a multidimensional assessment followed by individualised care, the so-called [G]OLD-protocol: ‘Getting OLD the healthy way’. Older people from control practices receive usual care (i.e., reactive care instead of proactive care). Effects on outcome measures are assessed at baseline (T_0_) and after 6-months (T_1_), 12-months (T_2_), and 18-months (T_3_) follow-up. Parallel to the effect study, a process evaluation is performed. Figure 1 presents a flow chart of the study design and measurements. A more complete overview of the study protocol, including a time schedule, is provided in Figure 2.

**Figure 1 F1:**
[figure not shown]
Flow chart study design and measurements.

**Figure 2 F2:**
[figure not shown]
**Schematic overview study protocol. **Note: PN = practice nurse; GP = general practitioner; IC = informed consent.

The Medical Ethical Committee (MEC) of the Maastricht University Medical Centre (MUMC+) judged this evaluation study as not needing formal ethical approval. Nevertheless, the MEC granted their approval for our study protocol and informed consent documents.

### Selection of general practices

General practices (n = 21) who visited older people at home as part of our pilot study [30] were excluded from participation to prevent contamination of prior experience. We approached 188 general practices in the three regions for participation in this study. Practices in Midden-Limburg were only invited to participate in the control group, since insufficient general practices from the other two regions were willing to participate in the control group. GPs who indicated to be actively engaged in or are planning to start with the identification and follow-up of frail older people in a systematic way were ineligible to participate (n = 12 practices). The availability of a practice nurse who has time for care for older people is a prerequisite for intervention practices. Practice nurses work in general practices, and provide screening, treatment, care and education mainly to patients with chronic diseases and older people.

Reasons of general practices for non-participation were: no time (e.g., due to other priorities, staff changes or participation in other research projects) (35.0%), no interest to participate in the present study (31.7%), interested in [G]OLD-intervention but not in research (19.5%), or no reason was mentioned (13.8%).

Fourteen general practices agreed to participate as intervention practice and 13 general practices consented to participate in the control group. Control practices were matched to intervention practices based on the presence of primary care professionals within general practices to ensure comparability at baseline. We assume that close proximity of various primary care disciplines facilitates collaboration in organising and/or delivering appropriate care to older people [31]. After the recruitment phase, one intervention practice and two control practices dropped out due to a lack of time to select older people eligible for participation. As a result, 24 general practices were included in this study.

### Target population

The target population are the apparently healthy, community-dwelling older people aged 75 years and older. Although the age criterion causes much controversy, especially from the age of 75 years on the prevalence of frailty increases markedly [32]. This enables us to find sufficient eligible older people for participation. Furthermore, some authors suggest that preventive home visits are most beneficial for people aged 75 years and older [33,34]. We excluded people who are not living independently, those on a waiting list for admission to a nursing home or home for older people, those under close medical supervision (chemotherapy, chronic haemodialysis or other therapies posing a high burden on the person), and the terminally ill. Practice nurses’ available working hours for care for older people determined the maximum number of older people that each of them was able to visit within one year's time. This, together with the size of the patient population aged 75 years and older, determined the number of older people per intervention practice approached for participation. In control practices, all eligible older people aged 75 years and over were approached.

We invited older people for participation by means of an information letter and consent form. We performed telephonic reminders in the intervention group and postal reminders after four weeks in the control group to those who did not respond to the first mailing.

### Procedure

Although the independent effects of components of preventive home visitation programmes are difficult to disentangle, previous research has suggested elements that at least should be included, such as a comprehensive geriatric assessment, a concrete care plan and multiple follow-up contacts [7,8,29]. We redesigned care delivery for older people by general practices by focussing on several evidence-based elements of the Chronic Care Model (CCM) and the Guided Care model (for details, see Figure 2). Applying both models has led to the development of the [G]OLD-protocol, which is explained in more detail below. Our pilot study provided preliminary evidence of the feasibility of the [G]OLD-protocol for general practices [30].

#### Training

Practice nurses from intervention practices received two days of training before the start of the study to provide them with the necessary knowledge and skills for executing all elements of the [G]OLD-protocol. In this way, we also attempted to equalise the level of knowledge and skills between practice nurses regarding care for older people. Central elements of the training included acquiring communication skills, gaining knowledge about frequently occurring health problems among older people, gaining knowledge about health services for older people, and learning how to assess older people’s physical, psychological, mental and social functioning by means of a multidimensional instrument. In between the two training sessions, each practice nurse performed exactly five home visits among randomly chosen older people (≥ 75 years) during a try-out phase. During the intervention period, sessions were organised for asking questions and exchanging experiences, and practice nurses received additional support by a coach specialised in geriatric care.

#### Home visit - comprehensive geriatric assessment

The practice nurse invites older people for a home visit successively within a one-year time period. Before the visit, the practice nurse makes a print out of the person’s medication list and medical history for relevant details or major events to be aware of.

During the visit, the practice nurse uses the [G]OLD-instrument: a structured, comprehensive geriatric assessment to assess the person’s physical, psychological, mental and social functioning, as well as lifestyle and medication use (see Table 1). This instrument is specifically developed for and tested among the apparently healthy community-dwelling older people aged 75 years and older in a pilot study [30]. Suggestions made during the pilot phase helped to improve the [G]OLD-instrument for application in the current longitudinal, quasi-experimental study. In general, the instrument assists the practice nurse in uncovering (early signs of) potential health problems or needs that may prevent older people, now or in the near future, from maintaining independent living. Although the instrument follows a structured format, it can be applied in a flexible way. For each test included, evidence-based cut-off points and guidelines are presented to assist in deciding about the presence or absence of health problems or needs.

**Table 1 T1:** **Topics included in the **[**G**]**OLD comprehensive geriatric assessment instrument**

	**Basic assessment –****part one**	**Additional assessment** – **part two**
Physical functioning and lifestyle	Disability in ADL and IADL; need for assistance in ADL and/or IADL; incontinence; mobility; falls; vision and hearing problems; BMI (height and weight); malnutrition; blood pressure; physical activity; smoking; alcohol use	N/A
Psychological functioning	Cognition; anxiety; depression; personality disorders	Cognition; depression; personality disorders
Social functioning	Receiving and providing informal care; loneliness; social participation	N/A
Additional	General perception of health and quality of life; medication use; financial situation; health care utilisation; observation of living environment; physical, psychological and behavioural signals	N/A

Note: N/A means not applicable.

Crucial during the visit is establishing a relationship of trust, listening to the needs and wishes of the older person, and allowing the person time to talk [29]. If necessary, the practice nurse may also provide information or advice. Sometimes it is necessary to perform an additional examination to obtain a more accurate estimation of the presence of problems. Therefore, more elaborate tests on the themes cognition, depression and personality disorders are incorporated in the [G]OLD-instrument part 2 which can be conducted during the first visit or during a second visit, depending on the older person’s preference.

After the home visit, the practice nurse registers the results of the [G]OLD-instrument in the electronic patient file.

#### Post-discussion GP and formulating care and treatment plan

The practice nurse discusses the results of the home visit with the GP. The results of the [G]OLD-instrument, as well as the patient’s needs and wishes, determine whether follow-up actions regarding certain problems are needed. These actions may consist of additional diagnosis, preventive care or advise, treatment in primary health care or referral to other care and/or well-being facilities as much as possible in the older person’s neighbourhood. The practice nurse formulates a provisional individualised care and treatment plan. This plan is discussed with the patient, whose input and wishes lead to a final care and treatment plan, which is registered in the electronic patient file.

#### Referral and follow-up

The practice nurse arranges and coordinates care for the older person as formulated in the final care and treatment plan and monitors the follow-up. The need for and frequency of follow-up contacts strongly depends on the type of problems or complaints that deserve attention according to the care and treatment plan. Hence, no fixed number of contacts per older person is determined on forehand. The practice nurse indicates in the care and treatment plan at what date a specific problem or complaint will be re-evaluated. Then, at each follow-up contact, the need for additional follow-up contacts is determined and, if necessary, the care and treatment plan is adjusted. Notably, these follow-up contacts may also take place with other care providers to whom older people are being referred.

If follow-up actions are not required or they are not desirable from the patient’s point of view, the practice nurse discusses with both the GP and the older person how they will proceed from that moment on. It is important that general practices should prevent to lose sight of their older patients after this initial assessment. The home visit is not meaningless when no specific problems are identified, as it helps to gain knowledge about the patient in case future health problems occur (e.g., falling incidents). Furthermore, the bond created with the practice nurse increases the likelihood that older people will approach their general practice in case of any future problems or complaints. Older people who do not receive follow-up contacts will remain part of the study population to ensure comparability with the control group and they will be analysed as a sub-group.

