### Statistical analyses

We compute descriptive statistics to describe the characteristics of the target population and general practices and to investigate comparability of study groups at baseline. Relevant statistical tests (e.g., t-test, chi-square, analysis of variance, regression analysis) will be applied to analyse effects on primary and secondary outcome measures (level of significance is 0.05; two-tailed). Data will be analysed according to the intention-to-treat principle. In all analyses, there will be a correction for possible baseline differences between participants or general practices. In addition, we will perform sub-group analyses to investigate whether certain groups of older people benefit more from the [G]OLD-protocol than other groups. We will use the software package SPSS for Windows, version 17.0, for all statistical analyses.

Data gathered as part of the process evaluation will be analysed using descriptive techniques, such as calculating scores (e.g., number of drop-outs), narrative description of procedures, and identifying themes in the interviews.

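### The planned sub-group of intervention patients without follow-up contacts is formed after baseline and has no control counterpart, so it cannot show who benefits

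*Protocol article*

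**What the plan says.** Under Referral and follow-up, the protocol article says that older people who receive no follow-up contacts "will remain part of the study population to ensure comparability with the control group and they will be analysed as a sub-group".

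Three statements show how a patient comes to be in that group:

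- Post-discussion GP and formulating care and treatment plan: the results of the home assessment, "as well as the patient’s needs and wishes, determine whether follow-up actions regarding certain problems are needed".
- Referral and follow-up: "The need for and frequency of follow-up contacts strongly depends on the type of problems or complaints that deserve attention".
- Referral and follow-up also covers patients for whom no follow-up is arranged: "If follow-up actions are not required or they are not desirable from the patient’s point of view", the nurse settles with the GP and the patient how to go on.

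The section on the home visit spreads the visits over a year. Study design and setting gives control patients usual, reactive care. Statistical analyses specifies intention to treat, a correction for baseline differences in every analysis, and, as an addition, "sub-group analyses to investigate whether certain groups of older people benefit more from the [G]OLD-protocol than other groups".

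**The concern.** A sub-group supports an effect estimate only if the same kind of person can be picked out in both arms, by something the intervention has not touched. This one fails on both counts. Membership is a product of the intervention process, and nothing in the control arm corresponds to it.

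The only purpose the article gives for sub-group analyses is to find who benefits more. A reader of the results would naturally place the no-follow-up group, or those who did get follow-up, next to the controls. A difference could then be taken as evidence that the visit alone helps, or that follow-up does not, when it reflects who needed or wanted follow-up.

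**Working it through.** **Step 1. Is membership a baseline variable?** No. It depends on the assessment, the discussion with the GP and the patient's wishes, all of which come after enrolment. With visits spread over a year, some patients may be classified after their 6-month or even 12-month questionnaire. How T0 is timed against each visit cannot be confirmed, because the schedule figure is not shown.

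**Step 2. Can controls be classified?** No. They have neither the assessment nor a care plan. The inputs to the decision are also largely unmeasured in them. Table 1 lists cognition, falls, incontinence, malnutrition, vision and hearing. The T0 questionnaire holds the RAND-36, the GARS, attitude to ageing, socio-demographic items and three utilisation items (Measures and data collection; Table 2).

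**Step 3. How large could selection be?** The article gives no size or expected effect for this sub-group, so there is no plan figure to reproduce. The following is an illustration with a true effect of zero.

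From Sample size considerations: SD = 21.2, and a target difference in mean change of 5.0. Assumed: share without follow-up q = 20%, 40% or 60%; correlation r = 0.3 between the assessment and the score, equal at T0 and at 18 months; correlation of 0.6 between the T0 and 18-month scores; the healthiest share q goes without follow-up.

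- Unadjusted shift against all controls = SD × r × φ(z)/q, with SD × r = 21.2 × 0.3 = 6.36.
- Baseline-adjusted shift, with slope 0.6 = unadjusted shift × (1 − 0.6).
- Change-score shift = SD × φ(z)/q × (correlation at 18 months − correlation at T0).

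| q | φ(z)/q | Unadjusted | Baseline-adjusted | Change score |
|---|---|---|---|---|
| 20% | 1.40 | 8.9 | 3.6 | 0 |
| 40% | 0.966 | 6.1 | 2.5 | 0 |
| 60% | 0.644 | 4.1 | 1.6 | 0 |

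A larger r raises these figures in proportion. At q = 20% and r = 0.7, simulation gives 20.8 points unadjusted and 8.3 adjusted.

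**Step 4. Does the zero for change scores hold generally?** Only if the assessment is equally related to T0 and 18-month health. Suppose instead that correlation decays with time, to 0.6 over 18 months, with q = 40% and r = 0.3 at the time of the visit.

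- Visit at T0: 21.2 × 0.966 × 0.3 × (0.60 − 1.00) = −2.5 points.
- Visit at month 12, with 0.6^(6/18) = 0.843 and 0.6^(12/18) = 0.711: 21.2 × 0.966 × 0.3 × (0.843 − 0.711) = +0.8 points.

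The baseline-adjusted shift moves too. It is 21.2 × 0.966 × 0.3 × (0.60 − 0.6 × 1.00) = 0 for a visit at T0, and 21.2 × 0.966 × 0.3 × (0.843 − 0.6 × 0.711) = 2.6 for a visit at month 12. Size, and for change scores sign, therefore depend on when visits happen and which analysis is used.

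**The case against.** The strongest reply is that the article plans no biased contrast. It says only that "they will be analysed as a sub-group", with no comparator, outcome or test. The mention of comparability with controls explains why these patients stay in the study population; it does not announce a sub-group comparison. The sentence can be read as a description within the intervention arm, and a condensed article may leave the comparator to the analysis plan. This stands. A reader might infer that a comparison with controls is laid down, and the text does not support that. Nor does Statistical analyses name this group among those to be examined for greater benefit. That examination is an additional analysis and not one of the study's main aims.

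Three further points also stand:

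- **Direction.** A reader might infer that the no-follow-up group must look better than controls. Patients who decline follow-up despite having problems belong to it too, and could pull the other way.
- **Size.** Setting 4 to 9 points directly against 5.0 is not like for like. The 5.0 is a difference in mean change, and every analysis is to be corrected for baseline. In the Step 3 illustration all three adjusted figures fall below 5.0.
- **Scope.** A reader might infer that the main comparison is compromised. It is not: these patients are already retained and analysed by intention to treat.

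The reply does not rescue the sub-group as a source of effect estimates. Baseline correction works only on what was measured at T0 in both arms, and much of what decides follow-up was not. The article commits to analysing the group, gives sub-group analyses a purpose that this group cannot serve, and does not limit its analysis to description.

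**Conclusion.** The point holds in conditional form. The article commits to analysing a sub-group whose membership is decided after baseline, within the intervention, and cannot be reproduced among controls. If that group or its complement is compared with controls, or used to say who benefits more, the result is not an intervention effect. That conclusion rests on the design text and does not depend on the sign or size of the bias.

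The size is illustrative only. With 20% to 60% without follow-up, a correlation of 0.3 and a baseline to 18-month correlation of 0.6, it is about 9 to 4 points unadjusted and 3.6 to 1.6 after baseline adjustment. For a pure change score it may be near zero. The share and both correlations are assumptions with no figure behind them in the article. The likely direction favours the no-follow-up group, but this is not certain. A purely descriptive summary within the intervention arm would be harmless.

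**What to change.** Two changes of wording:

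1. **Referral and follow-up:** keep the statement that these patients remain in the study population. Replace the sub-group commitment with a statement that patients without follow-up contacts are described within the intervention arm only, as part of the process evaluation, with no effect contrast against controls.
2. **Statistical analyses:** define effect sub-groups only by T0 variables collected in both arms (for example baseline GARS, age, household composition), and test each as an interaction with arm.

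This needs no new data, no more patients and no change in care. The cost is that no effect estimate is reported for patients who had the visit alone.
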